# Assessment of remifentanil for rapid sequence induction and intubation in patients at risk of pulmonary aspiration of gastric contents compared to rapid-onset paralytic agents: study protocol for a non-inferiority simple blind randomized controlled trial (the REMICRUSH study)

**DOI:** 10.1186/s13063-021-05192-x

**Published:** 2021-03-30

**Keywords:** Rapid sequence induction, Full stomach patient, Remifentanil, Paralytic agents, Succinylcholine, Rocuronium, Tracheal intubation

## Abstract

**Background:**

Rapid-onset paralytic agents are recommended to achieve muscle relaxation and facilitate tracheal intubation during rapid sequence induction in patients at risk of pulmonary aspiration of gastric contents. However, opioids are frequently used in this setting. The study’s objective is to demonstrate the non-inferiority of remifentanil compared to rapid-onset paralytic agents, in association with an hypnotic drug, for tracheal intubation in patients undergoing  procedure under general anesthesia and at risk of pulmonary aspiration of gastric contents.

**Methods:**

The REMICRUSH (Remifentanil for Rapid Sequence Induction of Anaesthesia) study is a multicenter, single-blinded, non-inferiority randomized controlled trial comparing remifentanil (3 to 4 μg/kg) with rapid-onset paralytic agents (succinylcholine or rocuronium 1 mg/kg) for rapid sequence induction in 1150 adult surgical patients requiring tracheal intubation during general anesthesia. Enrolment started in October 2019 in 15 French anesthesia units. The expected date of the final follow-up is October 2021. The primary outcome is the proportion of successful tracheal intubation without major complications. A non-inferiority margin of 7% was chosen. Analyses of the intent-to-treat and per-protocol populations are planned.

**Discussion:**

The REMICRUSH trial protocol has been approved by the ethics committee of The Comité de Protection des Personnes Sud-Ouest et Outre-Mer II and will be carried out according to the principles of the Declaration of Helsinki and the Good Clinical Practice guidelines. The results of this study will be disseminated through presentations at scientific conferences and publications in peer-reviewed journals. The REMICRUSH trial is the first randomized controlled trial powered to investigate whether remifentanil with hypnotics is non-inferior to rapid-onset paralytic agents with hypnotic in rapid sequence induction of anesthesia for full stomach patients considering successful tracheal intubation without major complication.

**Trial registration:**

ClinicalTrials.gov NCT03960801. Registered on May 23, 2019.

**Supplementary Information:**

The online version contains supplementary material available at 10.1186/s13063-021-05192-x.

## Introduction

Pulmonary aspiration of gastric contents is a severe complication related to general anesthesia, whose incidence increases in patients with a full stomach. Rapid sequence induction is recommended for patients at risk of pulmonary aspiration of gastric contents (for example, emergency procedure, bowel obstruction, obese patients, or severe gastroesophageal reflux). Standard rapid sequence induction relies on the combination of a rapid hypnotic drug with a rapid-onset paralytic agent. In this setting, succinylcholine is recommended as the rapid-onset paralytic agent of first intention [1]. However, several severe adverse events are frequently reported with this drug, especially anaphylactic reaction, extended neuromuscular block, malignant hyperthermia, and severe hyperkalemia [2]. In case of counterindications of succinylcholine use, a high-dose of rocuronium, another rapid-onset paralytic agent, is recommended [3]. Unfortunately, rocuronium causes as many anaphylactic events as succinylcholine (1 anaphylactic event for 3000 uses) and induces a protracted neuromuscular blockade which frequently exceeds the duration of the surgical procedure [4]. Despite international guidelines, and probably due to safety concerns, rapid-onset paralytic agents are only used in 31 to 55% of rapid sequence induction [5–8].

When rapid-onset paralytic agents are not used for rapid sequence induction, opioids are frequently associated with hypnotics during the intubation procedure. Remifentanil, which is the opioid with the shortest delay and duration of action [9], has been proposed as an alternative to paralytic agents during rapid sequence induction. Several studies have shown that the use of remifentanil is associated with similar conditions of tracheal intubation and fewer hemodynamic reactions compared with neuromuscular blockade agents during scheduled surgery [10–14]. However, the risk of major complications during rapid sequence induction performed with remifentanil has not yet been thoroughly compared to rapid-onset paralytic agents.

We hypothesized that remifentanil associated with a hypnotic drug is not inferior to rapid-onset paralytic agents with a hypnotic drug for rapid sequence intubation for patients at risk of pulmonary aspiration of gastric contents and requiring general anesthesia for surgical procedure.

We thus designed the REMICRUSH (Remifentanil for Rapid Sequence Induction of Anaesthesia) trial, which is a multicenter, single-blinded, non-inferiority randomized controlled trial comparing remifentanil (3 to 4 μg/kg) with rapid-onset paralytic agents (succinylcholine or rocuronium 1 mg/kg) for rapid sequence induction in 1150 adult patients at risk of pulmonary aspiration of gastric contents needing orotracheal intubation under general anesthesia.

## Methods and design

### Hypothesis

The incidence of major complications during the tracheal intubation of patients at risk of pulmonary aspiration of gastric contents is not increased by remifentanil use, as a replacement for rapid-onset paralytic agents (succinylcholine or rocuronium), in intravenous rapid sequence induction and intubation.

### Research questions

Is remifentanil, in association with a hypnotic, non-inferior to rapid-onset paralytic agents considering successful tracheal intubation without major complications?Does remifentanil use in rapid sequence induction allow similar conditions for tracheal intubation in patients at risk of pulmonary aspiration of gastric contents than rapid-onset paralytic agents?Does remifentanil use in rapid sequence induction reduce the risk of postoperative respiratory complications?

### Design

The REMICRUSH (Remifentanil for Rapid Sequence Induction of Anaesthesia) trial is an investigator-initiated, multicenter, single-blinded, non-inferiority randomized controlled clinical trial.

### Ethics

The Comité de Protection des Personnes Sud-Ouest et Outre-Mer II (France) approved the study protocol (version 1.1, July 4, 2019). Patients provide written consent for participation when possible. Patients are eligible to be enrolled without legal surrogate consent if they cannot express consent due to the emergency situation and if next of kin cannot be informed in the maximal delay for inclusion. Patients who recover sufficient capacity to provide consent will be asked to consent to continue participation in the trial (model consent form and other related documentation given to participants and authorized surrogates are available in Additional file 6; in French). As we have not planned any further ancillary studies, no additional consent provisions for the collection and use of participant data and biological samples have been provided.

The REMICRUSH study is conducted under the declaration of Helsinki and is registered on May 2019 at http://clinicaltrials.gov/ with trial registration NCT03960801 (Supplemental Table S1).

## Methods

### Study population

Patients, aged from 18 to 80 years old, seen by investigators in planned anesthesia consultations or during their admission to the operating room and who will have a surgical or interventional procedure under general anesthesia with tracheal intubation and considered at risk of pulmonary aspiration of gastric contents may be offered to participate to the study. The risk of pulmonary aspiration of gastric contents was defined by at least one of the following criteria: pre-operative fasting period less than 6 h, occlusive syndrome, functional ileus, vomiting episode within the last 12 h, orthopedic trauma within the last 12 h, medical history of symptomatic gastroesophageal reflux or hiatus hernia or gastroparesis or dysautonomia or gastroesophageal surgery with sphincter dysfunction.

Patients who met any of the following criteria will be excluded from the study: pregnant women, contraindication to any rapid-onset paralytic agent (known allergy to rapid muscle relaxant drugs, personal or family history of known malignant hyperthermia, congenital muscular dystrophy, myasthenia, a known congenital deficit in plasma pseudocholinesterase), intended use of etomidate as hypnotic to induce anesthesia, prediction of impossible tracheal intubation, pre-operative respiratory failure (SpO_2_ < 95%), pre-operative hemodynamic failure (mean arterial pressure under 65 mmHg or use of vasopressor), patient in cardiac arrest, patient under justice protection, and the absence of affiliation with French social security system.

The modalities for obtaining patient consent by Investigating Physicians are described in the “Ethics” section.

### Setting

The study involves 15 French anesthesia units from university and non-university hospitals, each center caring for emergency and non-emergency anesthetic procedure (by alphabetic order: Angers University Hospital, Brest University Hospital, Clermont-Tonnerre Military Hospital, Grenoble University Hospital, La Roche-sur-Yon Public Hospital, Le Confluent Private Hospital, Le Mans Public Hospital, Lille Huriez University Hospital, Lille Salengro University Hospital, Lyon Sud University Hospital, Nantes Hotel-Dieu University Hospital, Nantes Laennec University Hospital, Toulouse Purpan University Hospital, Toulouse Rangueil University Hospital, Valenciennes Public Hospital).

### Treatment allocation

Randomization was performed through a secure web-based randomization system. The randomization list was generated by a statistician, not involved in determining the eligibility or the assessment of outcomes. The sequences were generated using the PROC PLAN procedure from SAS, version 9.4 (SAS Institute), and the statistician was the only one who knows size of the randomization blocks. Patients are randomized to the remifentanil (intervention group) or the rapid-onset paralytic agent (control group) in fixed blocks, in a 1/1 ratio, with stratification based on the type of laryngoscopy (direct vs. indirect video-laryngoscope, which is a risk factor of successful intubation at the first attempt) and on digestive occlusive syndrome (yes or no, which is a significant risk of gastric inhalation) (Fig. 1).

**Fig. 1 Fig1:**
[figure not shown]
CONSORT diagram of the Remifentanil for Rapid Sequence Induction of Anaesthesia (REMICRUSH) trial illustrating the randomization and flow of patients in the study

### Masking protocol

It is not possible to blind local investigators to allocation as it is obvious clinically which patients are receiving rapid-onset paralytic agents. Patients are blinded to the group allocation as well as the data analysts.

### Procedures

The choice of hypnotics is at the physician’s discretion with dosage based on estimated patient weight and height. The injection of the hypnotic is followed immediately by an intravenous bolus of either remifentanil (3 to 4 μg/kg) in the intervention group or rapid-onset paralytic agent (1 mg/kg of succinylcholine or 1 mg/kg of rocuronium at the physician’s discretion) in the control group, with weight adjustment according to the body mass index (Supplemental Table S2). It is recommended to perform the tracheal intubation 30 to 60 s after administering the paralytic agent or the remifentanil. In the rapid-onset paralytic agent group, no opioid is injected before the tracheal intubation. In case of difficult unplanned intubation, the physicians are free to use a rapid-onset paralytic agent or remifentanil as rescue therapies (Fig. 2).

**Fig. 2 Fig2:**
[figure not shown]
Data collection timeline for the REMICRUSH study. FeO2, fractional expired oxygen concentration, ROP, Rapid-Onset Paralytic Agent

### Standard care

Anesthesiologists are asked to follow the French guidelines for sedation and analgesia in the operating room. A trained anesthesiologist performs the tracheal intubation (> 4 semesters of training in anesthesiology for residents) or nurses specialized in anesthesiology (> 2 years of practice). In both groups, sedation induction is performed after preoxygenation (target FeO_2_ > 80%). The choice of laryngoscopes’ device (single-use Macintosh metallic laryngoscope blades (size 3 or 4) or video laryngoscopy) is at the physician’s discretion defined before randomization (criteria of stratification of the randomization). The uses of alternative airway procedures (for instance, stylet, backward, upwards, and rightwards pressure “BURP” maneuver or Sellick maneuver) are allowed. In case of major and minor complications associated with the study intervention, general anesthesia, or surgical procedure, post-trial care will comply with national and local protocols as appropriate. Especially in case of first intubation failure, an alternative procedure including the use of video laryngoscopy, gum elastic bougie, intubating laryngeal mask airway, or trans-cricothyroid oxygenation technique is recommended under the French guidelines on difficult airway management [15]. Hypotension is managed via fluid resuscitation with crystalloids and ephedrine, and prolonged hypotension is treated with continuous intravenous catecholamine administration [16].

### Protocol drop-out

Patients not receiving the attributed drugs or receiving the other study drug as rescue therapy for non-predicted difficult intubation will be kept in analysis and remain analyzed with their randomized group.

### Study endpoints

The primary endpoint is the proportion of patients with successful tracheal intubation without any significant complications up to 10 min after induction of anesthesia. Major complications during the first 10 min after induction of anesthesia are defined as the failure of tracheal intubation at the first attempt, pulmonary aspiration of gastric contents, oxygen desaturation < 95%, severe hemodynamic instability (mean arterial pressure (MAP) ≤ 50 mmHg or ≥ 110 mmHg for more than 3 min), severe arrhythmia (i.e., requiring pharmacological or electrical intervention or lasting more than 30 s), ventricular fibrillation or cardiac arrest, and anaphylactic reaction grade III or IV in HAS classification.

Secondary endpoints which will be compared between the two study groups are as follows:

In the operating theater: median intubation quality score (IDS-3 score) values [17], Cormack-Lehane (Supplemental Figure S1) and median POGO score values [18], percentage of patients requiring tracheal intubation alternative technique, median time between the administration of the hypnotic (start of anesthetic induction) and tracheal intubation (defined as the 6th capnography curve), median minimal value of SpO_2_ value within the first 10 min after anesthesia induction, percentage of patients with moderate desaturation (SpO_2_ ≤ 95%) or severe (SpO_2_ < 80%) within the first 10 min after anesthesia induction, percentage of patients with a severe hemodynamic disorder within the first 10 min after anesthesia induction (heart rate lower than 45 beats per minute (bpm) and/or higher than 110 bpm and/or a systolic blood pressure (SBP) lower than 80 mmHg and/or a SBP higher than 160 mmHg and/or a MAP of less than 55 mmHg and/or a MAP higher than 100 mmHg), frequency of patient with dental or tracheal injury during general anesthesia, frequency of patients with an allergic event of HAS 2013 grade I or II during general anesthesia, and the median doses of vasopressors used after induction,

In the recovery room: postoperative Sore Throat Score median values [19], percentage of patients with nausea, vomiting, aspiration of gastric contents, percentage of patients with laryngeal dyspnea, percentage of patients with SpO_2_ ≤ 92, percentage of patients with SpO_2_ < 80%, percentage of patients requiring post-extubation respiratory support, proportion of reintubation, and proportion of postoperative emergency ICU admission.

After discharge of the recovery room: percentage of patients with postoperative pneumonia diagnosed up to day 7 and defined by the presence of new or progressive infiltrate on chest X-ray or C.T. scan, associated with any of the following symptoms: onset of purulent sputum, change in the appearance of chronic sputum, fever ≥ 38 °C, hyperleukocytosis (> 12,000/mL) or leukopenia (< 4000/mL), positive blood cultures or isolation of the pathogen on sputum, tracheal aspiration or bronchoalveolar lavage, percentage of patients with acute respiratory failure occurring up to day 7 defined by the combination of a clinical picture of acute hypoxemic respiratory failure, a PaO_2_/FiO_2_ ratio < 300 mmHg, the presence of new bilateral pulmonary infiltrates on the chest X-ray and the absence of evidence of cardiac origin, intra-hospital mortality up to day 7, and survival proportion at day 7.

Proportion of adverse events will be compared between the study groups. All expected and unexpected serious adverse events, as defined as EMA grade 3 (severe), 4 (life-threatening), to 5 (lethal), will be systemically recorded on day 1 and day 7. The proportion of expected and unexpected serious adverse events will be analyzed and reported in future publications.

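### In-theater aspiration after minute 10, in-theater reintubation and late grade III–IV anaphylaxis have no dedicated endpoint, and the allergy endpoint follows mild reactions longer than severe ones

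*Protocol article*

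**What the plan says.** The primary endpoint, in Study endpoints, is the proportion of patients with "successful tracheal intubation without any significant complications up to 10 min after induction of anesthesia". Its components carry the same window: "Major complications during the first 10 min after induction of anesthesia are defined as the failure of tracheal intubation at the first attempt, pulmonary aspiration" and further items, the last of which is "anaphylactic reaction grade III or IV in HAS classification".

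The secondary endpoints are grouped by place, and several items carry their own window. In the operating-theater list, the oxygen saturation and hemodynamic items are limited to the first 10 minutes, whereas dental or tracheal injury and allergy run through general anesthesia. The allergy item reads "frequency of patients with an allergic event of HAS 2013 grade I or II during general anesthesia". This list has no aspiration item and no reintubation item.

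The recovery-room list includes "percentage of patients with nausea, vomiting, aspiration of gastric contents" and, further on, reintubation. Pneumonia and acute respiratory failure are followed to day 7.

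Study endpoints closes with general safety reporting: "Proportion of adverse events will be compared between the study groups". Serious adverse events of grade 3 to 5 are recorded on day 1 and day 7, analyzed and reported.

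Under Pre-planned primary analysis, the paragraph on secondary endpoints assigns Poisson regression to a count of allergic episodes. It states neither grade nor period.

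**The concern.** Read together, the windows leave an interval between minute 10 and the recovery room in which three kinds of event have no endpoint of their own: aspiration (including at extubation in theater), reintubation in theater, and grade III–IV anaphylaxis.

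These events matter to the trial's own rationale. The Discussion names aspiration among the major complications that induction in a non-fasting patient is meant to limit. The Introduction gives anaphylaxis and prolonged block as reasons to look for an alternative to paralytic agents, and says that rocuronium's block often outlasts surgery. Any airway effect of residual block would be expected at emergence, part of which takes place in theater.

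The allergy item has a second problem. Severity and window run in opposite directions, so on the named endpoints a mild late reaction is an event and a life-threatening one is not.

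**Working it through.** **1. The named endpoints by period.** All entries come from Study endpoints.

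| Event | Induction to minute 10 | Minute 10 to leaving theater | Recovery room |
|---|---|---|---|
| Aspiration | primary component | none | secondary |
| Reintubation | none | none | secondary |
| Allergy, grade I–II | secondary | secondary, while under general anesthesia | none |
| Anaphylaxis, grade III–IV | primary component | none | none |

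Take a reaction at minute 12. At grade II it counts in the allergy endpoint. At grade IV it counts neither there (wrong grade) nor in the primary composite (too late).

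**2. What the general safety reporting adds.** The comparison of adverse events states no time limit and no grade threshold, so it can include all of these events. It is a pooled proportion, however, and isolates neither aspiration nor anaphylaxis. Systematic recording is stated only for serious events of grade 3 to 5. A lower-grade aspiration in theater at minute 15 would enter only the pooled figure.

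**3. The allergy definition in two places.** Study endpoints counts patients with a grade I–II event. The analysis section counts episodes, with no grade and no window. The two differ in unit and possibly in grade, and the document does not say which governs.

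**4. The plan's own figure.** Sample size gives 575 per group for 80% success, a 7% margin, 80% power and an alpha of 2.5 (read as 2.5% one-sided). The pooled two-proportion formula with 0.80 and 0.73 (mean 0.765) reproduces it:

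n = [1.960·√(2·0.765·0.235) + 0.842·√(0.80·0.20 + 0.73·0.27)]² / 0.07² = 575 per group.

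The endpoint windows do not enter this formula. The figure serves below only as a denominator.

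**5. Expected numbers.**
- Anaphylaxis: the Introduction gives 1 per 3000 uses. Expected among controls: 575/3000 = 0.19. Chance of at least one: 1 − (1 − 1/3000)^575 = 0.17. This covers reactions at any time, so fewer are expected after minute 10.
- Aspiration after minute 10: the document gives no rate. Assuming 0.2% to 1%, 575 × 0.002 = 1.2 and 575 × 0.01 = 5.8, or about 1 to 6 patients per arm.
- Reintubation in theater: the document gives no rate, and none is assumed here.

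**The case against.** A reader might infer from the table that these events are counted in no endpoint at all. The document does not support that. The adverse-event comparison stands in the same section, is made between the groups, and has no stated window. A late grade III–IV anaphylaxis, or an aspiration with serious effects, would plausibly fall under the grade 3–5 report as well. Pneumonia and acute respiratory failure to day 7 pick up serious consequences of an aspiration whenever it occurred. The unrestricted count of allergic episodes may also include severe reactions.

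A reader might also infer that the third research question ("Does remifentanil use in rapid sequence induction reduce the risk of postoperative respiratory complications") goes unanswered. It asks about postoperative complications, and the recovery-room and day-7 endpoints address much of that. Nor does it follow that patients taken straight to intensive care are lost. Emergency ICU admission is itself an endpoint and the day-7 outcomes still apply. Where such patients are assessed for recovery-room items may be left to the full protocol.

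Two further objections have weight. The ten-minute window suits a trial of drugs given as a bolus at induction. The recovery-room heading might also mark when data are collected, since Follow-up data says the collection sheet is completed there.

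These arguments limit the point but do not remove it. The place-of-collection reading does not explain the allergy item, where both window and grade are explicit. Nor is this just an article's brevity, because the section distinguishes the first 10 minutes from the whole anesthetic item by item. The day-7 outcomes record consequences, not the aspiration itself.

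**Conclusion.** The point holds in a limited form. Aspiration in theater after minute 10, reintubation in theater, and grade III–IV anaphylaxis after minute 10 have no dedicated endpoint and are reached only through pooled adverse-event and serious-adverse-event reporting. The allergy secondary endpoint is inverted by severity, and the analysis section does not settle what is counted.

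The primary endpoint, its analysis and the sample size are not affected. The expected gain is modest: about 0.19 control-arm anaphylactic events at the protocol's own rate, and about 1 to 6 late aspirations per arm on an assumed 0.2% to 1%. The case therefore rests on coherent definitions and readable safety results, not on power. It assumes that the place headings delimit what is counted. If they mark only the point of collection, the aspiration and reintubation gap narrows, but the allergy inversion remains.

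**What to change.** Leave the ten-minute primary window as it is. Amend the secondary definitions:

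- Aspiration of gastric contents: from induction to recovery-room discharge, reported separately before and after minute 10.
- Reintubation: from first extubation, whether in theater or in the recovery room.
- Allergic events: grades I to IV during general anesthesia, reported by grade.

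Then align the analysis section with the allergy definition by stating whether patients or episodes are counted, with which grades and over which period.

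The cost is revised endpoint wording and a few extra eCRF fields completed from the anesthesia record. No additional visit, procedure or patient is needed.

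### The secondary severe haemodynamic disorder endpoint counts low and high values as one event, so opposite shifts in the two arms can offset and hide an excess of low-side events

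*Protocol article*

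**What the plan says.** All references are to the protocol article.

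- **Study endpoints, secondary, operating theatre.** The endpoint is a single proportion: "percentage of patients with a severe hemodynamic disorder within the first" 10 minutes after induction. The criteria run "heart rate lower than 45 beats per minute (bpm) and/or higher than 110 bpm and/or a systolic blood pressure (SBP) lower than 80 mmHg" and continue with "a SBP higher than 160 mmHg and/or a MAP of less than 55 mmHg and/or a MAP higher than 100 mmHg". They are joined by and/or, so one crossing in either direction makes the patient an event.
- **Study endpoints, primary.** One component of the composite also has a low and a high limit: "severe hemodynamic instability (mean arterial pressure (MAP) ≤ 50 mmHg or ≥ 110 mmHg for more than 3 min".
- **Procedures.** The hypnotic "is followed immediately by an intravenous bolus of either remifentanil" in the intervention arm or a paralytic agent in the control arm. For the control arm: "In the rapid-onset paralytic agent group, no opioid is injected before the tracheal intubation".
- **Introduction.** Earlier studies of remifentanil are summarised as showing "fewer hemodynamic reactions compared with neuromuscular blockade agents during scheduled surgery". The direction of those reactions is not given.
- **Other planned haemodynamic information.** Median vasopressor dose is a separate secondary endpoint (Study endpoints). Heart rate and systolic pressure are named as continuous variables for linear regression (Pre-planned primary analysis, paragraph on secondary endpoints). Proportions of adverse events are compared between groups (end of Study endpoints).

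**The concern.** A two-directional composite does little harm when the treatments push both tails the same way. Here the arms differ, by design, in whether an opioid is present at laryngoscopy. It is foreseeable that one arm has more values below the low limits and the other more values above the high limits. The endpoint scores a systolic pressure of 75 mmHg and one of 165 mmHg identically, so an increase in one tail is offset by a decrease in the other.

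At stake is what the trial can say about haemodynamic tolerance. The Discussion presents remifentanil as a possible alternative to paralytic agents if non-inferiority is shown. A pooled comparison near zero, or one favouring remifentanil, could be reported as reassuring while the share of patients with severe low values was higher. The reverse error, missing fewer high-side events, is equally possible.

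**Working it through.** **Figure in the plan.** None is stated for this endpoint, and no low-side or high-side rates appear anywhere. The only planned number used below is the group size of 575 (Sample size). That figure can be reproduced by comparing 80% with 73%, two-sided 5%, 80% power, pooled variance: (1.960 × √(2 × 0.765 × 0.235) + 0.842 × √(0.80 × 0.20 + 0.73 × 0.27))² / 0.07² = 574.8, rounded up to 575. It is not in dispute here.

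**Formulas.** Let L and H be the proportions with a low-side and a high-side event.
- If no patient has both, the pooled proportion is L + H.
- If the two occur independently, it is 1 − (1 − L)(1 − H).
- Difference d = p_R − p_C (remifentanil minus control), with 95% CI d ± 1.96 × √[(p_R(1 − p_R) + p_C(1 − p_C)) / 575].

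**Illustration A (assumed rates, chosen to offset exactly): L 12% vs 6%, H 14% vs 20%, remifentanil vs control.**
- Low: SE = √[(0.12 × 0.88 + 0.06 × 0.94) / 575] = 1.68 points; d = +6.0 (2.7 to 9.3).
- High: SE = √[(0.14 × 0.86 + 0.20 × 0.80) / 575] = 2.21 points; d = −6.0 (−10.3 to −1.7).
- Pooled, exclusive events: 26% vs 26%; SE = √[2 × 0.26 × 0.74 / 575] = 2.59 points; d = 0 (−5.1 to +5.1).
- Pooled, independent events: 1 − 0.88 × 0.86 = 24.3% vs 1 − 0.94 × 0.80 = 24.8%; d = −0.5 (−5.5 to +4.5).

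Both tails differ by intervals that exclude zero, and the pooled endpoint shows nothing.

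**How the result moves with other assumed rates (exclusive events).**

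| Case | Low, R vs C | High, R vs C | Pooled, R vs C | Pooled d (95% CI) | Low-side d (95% CI) |
|---|---|---|---|---|---|
| A | 12% vs 6% | 14% vs 20% | 26% vs 26% | 0 (−5.1 to 5.1) | +6 (2.7 to 9.3) |
| B | 15% vs 5% | 20% vs 40% | 35% vs 45% | −10 (−15.6 to −4.4) | +10 (6.6 to 13.4) |
| C | 20% vs 10% | 12% vs 15% | 32% vs 25% | +7 (1.8 to 12.2) | +10 (5.9 to 14.1) |

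In B the pooled endpoint favours remifentanil although low-side events triple. In C the opposing shift is small and the pooled endpoint still points the right way, but understates the low-side excess. Cancellation is therefore possible but not inevitable.

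**The case against.** The strongest reply has four parts.

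1. **Low-side harm is not invisible elsewhere.** Median vasopressor dose mainly reflects hypotension, severe arrhythmia needing intervention is part of the primary composite, adverse events are compared, and the monitoring board reviews safety every 400 inclusions. This stands, and it limits the consequence. None of these, however, yields the proportion with severe low or high values. A median dose can be zero in both arms if fewer than half the patients are treated.

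2. **The linear model of systolic pressure would reveal the shift.** Suppose, for illustration, that systolic pressure alone drives case A and is normal with limits 80 and 160.
   - Control: SD = 80 / (1.555 + 0.842) = 33.4, mean = 80 + 1.555 × 33.4 = 131.9.
   - Remifentanil: SD = 80 / (1.175 + 1.080) = 35.5, mean = 80 + 1.175 × 35.5 = 121.7.
   - The difference is 10.2 mmHg with SE √[(33.4² + 35.5²) / 575] = 2.03, so z is about 5.

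   The direction would indeed show. But a remifentanil mean of 121.7 is equally compatible with no low-side excess: with SD = 41.7 / 1.555 = 26.8, 6% fall below 80 and P(Z > 38.3 / 26.8) = 7.6% exceed 160. The same mean difference fits either more hypotension or only less hypertension.

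3. **The rates are invented.** Correct. They show what the definition permits, not what is likely.

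4. **Component reporting belongs in an analysis plan that is not shown, and a net burden of extremes is a legitimate measure.** Partly right. The pooled endpoint may stay, and tabulating components of the primary composite can be left to that plan. But the endpoint to be compared is defined in this document, and it is the pooled one.

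**Conclusion.** The structural point holds: as defined, the endpoint can return a null or favourable result while severe low-side events are more frequent with remifentanil. How far this would happen cannot be computed from the documents. The 6-point low-side difference behind a pooled zero is an assumed example at 575 per arm. Near-complete cancellation needs roughly equal and opposite shifts, and it survives whether the events are exclusive or independent.

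Three stronger readings are tempting and not supported.

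- A reader might infer that the trial could not detect or report hypotension or bradycardia at all. The other planned comparisons give partial directional information.
- A reader might infer that the protocol itself expects excess hypotension as the main dose-related harm. No section says so. The Introduction mentions only "fewer hemodynamic reactions compared with neuromuscular blockade agents during scheduled surgery", without direction and in scheduled surgery.
- A reader might infer that the primary composite must change because its MAP component is also two-sided. It counts intubations free of any major complication, and nothing here affects its margin, sample size or decision rule.

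This is a worthwhile correction to one secondary endpoint. It does not threaten the primary conclusion.

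**What to change.** Keep the pooled endpoint if it is wanted as a net measure. Beside it, pre-specify two binary secondary endpoints over the same 10 minutes, using only the limits already printed:

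- **Low:** HR <45 bpm and/or SBP <80 mmHg and/or MAP <55 mmHg.
- **High:** HR >110 bpm and/or SBP >160 mmHg and/or MAP >100 mmHg.

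A patient may count in both. Compare each between arms with the logistic model already planned for binary secondary endpoints, and report the difference in proportions with its 95% CI. State that any conclusion on haemodynamic tolerance rests on these two results and not on the pooled figure. Leave the primary composite as it is.

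The cost is wording and one or two more secondary comparisons. The pooled endpoint already needs each of these limits to be assessed, so no new measurement should be required. The case report form is not shown, so confirm that it records which limit was crossed. Make the change before any comparison by arm is seen, because a split chosen afterwards would be post hoc.
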